
##### Stage 4: Health education model enhancement and promotion

An agent-based simulation model that considers human mobility in HK will be developed [36]. The model will be trained using data from the 24 community-based intervention programmes, to establish the most optimal community-based health education model(s) for COVID-19 prevention. We assume different intervention programmes will cause different changes in the vaccine uptake patterns among participants. Each intervention programme’s result (e.g., the vaccine uptake number) will be collected for comparison purposes. Then, the programme with maximal vaccine uptake and minimal healthcare requirements (e.g., number of infections detected) will be chosen as the most optimal strategy. Once the simulation modelling is completed, a toolkit book that contains (1) training workshop content and (2) details on the implementation and assessment of the most optimal health education model(s) will be produced and disseminated to additional NGOs, companies and schools. A health education pamphlet containing relevant COVID-19 information and the successful experiences of our health education programmes will be disseminated to the public via the research partners within one year. We expect that 200 NGOs, companies and schools will be approached, and 20,000 HK residents will receive the pamphlets. In addition, several press conferences will be held to share our findings and experiences with the public.

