### 7.1. Aims

The ultimate goal of the proposed study is to mitigate COVID-19 risk in HK communities. Objective 1: To equip community partners with the knowledge and skills necessary to design and implement appropriate interventions for COVID-19 prevention. Objective 2: To carry out community-based education programmes for improving early testing for COVID-19, increasing vaccination rate and enhancing self-protection measures against COVID-19 in HK. Objective 3: To determine the most sustainable and suitable community education model and use it on a large scale across different communities. 

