Sample size: As a cluster RCT, the randomization is conducted in the cluster level. In our study, each cluster is a group of participants recruited by the same research partner. In our study, based on our simulation modelling [32], a 20% increase in the vaccination rate could have significant social benefit. With conventional assumptions of a two-sided 5% significance level and assuming an intra-cluster correlation of 0.01, we would have 86% power to detect a difference of 20% if there are 50 participants in each cluster and 8 clusters in each sector [33]. Thereby 3 sectors will have 3 × 8 = 24 clusters and 1200 participants in total. For each sector, 8 clusters (400 participants) will be evenly divided into either the intervention group or the control group. When we used the same method to calculate the sample size for detecting 20% difference in the percentage of early testing (another primary outcome), the sample size was smaller than the previous one. We thereby consider the former one as our final sample size, as it could ensure the power of the study.

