##### Stage 3: Implementing the Community-Based Health Education Programmes

Design and setting: stage 3 is a multicentre cluster RCT. The intervention programmes will be implemented by the research partners. 

Randomisation and concealment: The participants recruited by one research partner will be considered as one cluster. A research assistant will randomly assign the clusters from the NGOs, Schools, and Companies to either the intervention group or the control group, respectively. Concealment of the allocation sequence to the investigators will be done until assignment occurs. After allocation, there will be four clusters in both the intervention and control groups from the NGOs, schools and companies, respectively. This will result in 3 × 4 = 12 clusters for each group (intervention/control). An active wait-list control group will be used instead of a standard control group to help motivate the collaborators to implement the programme and to avoid a high participant dropout rate. Intervention: The core intervention package will potentially include the following four components. (1) A manual of self-protection against COVID-19 infection. The main content will include hand washing, mask wearing and social distancing guidelines. (2) Early testing. Participants will be trained on how to recognize the early symptoms of COVID-19 and appropriate practice to take in a response, and they will be provided with testing resources. The COVID-19 Rapid Antigen Test (RAT) will be provided to participants as an incentive to facilitate self-testing at home. This RAT is a lateral-flow immunoassay designed for the qualitative detection of SARS-CoV-2 antigens in nasal swab samples. (3) Knowledge of vaccines and their benefits and resources for vaccination. (4) Post-vaccination follow-up. Participants will be trained on how to recognise vaccine side effects and to provide further protection measures, and they will be provided with resources for consultation and treatment. The research partners will design the community-based education programmes (based on the core intervention) after the TTT workshop. They will be required to submit a brief standardized proposal to the academic investigators for review and approval, to ensure that all intervention programmes have the same core intervention contents and can be implemented appropriately. The development and implementation of the intervention will follow the procedures outlined in the PROCEDE-PROCEED model (Figure 2). Research partners will be able to use any reasonable strategies, such as social media platforms, information technology, posters, leaflets, and videos, to implement the programmes. Each programme will last for 3 months. The active wait-list control group will undergo parallel assessment at the same time points as the intervention group, while the core intervention contents will be delivered after 3 months. We expect that the 24 intervention programmes will be completed within 2 years. Evaluation: Evaluations will be conducted at baseline (T_0_), middle term (T_1_, 1.5 months), and at the end of the trial (T_2_, 3 months). Participants’ knowledge, attitudes and behaviours towards COVID-19 prevention will be evaluated using a self-designed questionnaire, based on the KAP model. In addition, a process evaluation that determines whether the programme is being implemented as intended will be performed as follows. Every month, the academic investigators and the collaborators will review the progress of each programme together. Information on the attendance rate of each programme and feedback from program participants and research partners will also be evaluated qualitatively. A flow chart of the all the data collection steps is shown in Figure 3.

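### Study 1 Stage 4 selects one of 24 programmes of about 50 people on observed uptake and infections detected, a rule that at the planned ICC finds the truly best programme only about a quarter of the time

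*Protocol article*

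**What the plan says.** Stage 4 of Study 1 (Protocol article, section 7.2.2) builds an agent-based simulation: "The model will be trained using data from the 24 community-based intervention programmes". Each programme's result is gathered, with the example given as "the vaccine uptake number) will be collected for comparison purposes". The operative rule follows: "the programme with maximal vaccine uptake and minimal healthcare requirements (e.g., number of infections detected) will be chosen". Details of the selected model or models then go into a toolkit for further organisations.

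The size of each programme comes from the sample-size paragraph in section 7.2.1, which claims 86% power for a 20% difference between arms "if there are 50 participants in each cluster and 8 clusters in each sector", with an ICC of 0.01. Section 7.2.3 defines the vaccination rate as vaccinated participants over all participants, which is a level and not a change. The mixed models described there serve the two-arm Stage 3 comparison, not the choice among programmes.

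Stage 3 requires the same core content in every programme, supplies rapid antigen tests for home use, and delivers the content to wait-list clusters after 3 months. The last stated assessment is also at 3 months. On timing it adds: "We expect that the 24 intervention programmes will be completed within 2 years". Objective 2 in section 7.1 begins: "To carry out community-based education programmes for improving early testing for COVID-19".

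**The concern.** The trial is sized to compare two arms. Stage 4 uses the same data for a much harder task, naming the best of 24 small groups. Taking the maximum of many noisy rates favours whichever group was lucky. Because the rate is a level, it also favours groups that were already well vaccinated. The clusters come from NGOs, companies and schools, and there is no reason for their starting uptake to match.

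The second criterion treats fewer detected infections as better. The package sets out to raise testing, and more testing finds more infections. The text does not say how the two criteria are traded off when they disagree.

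What is at stake is Objective 3, the choice of a community education model for wider use. The Stage 3 comparison of arms is not affected.

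**Working it through.** **The plan's own figures.** 3 sectors × 8 clusters × 50 = 1,200 participants, as stated. The design effect is 1 + 49 × 0.01 = 1.49, so each arm within a sector has 200/1.49 = 134.2 effective participants. A t-test on 6 degrees of freedom gives power from 79.5% (40% vs 60%) to 86.0% (20% vs 40%, or 60% vs 80%). The stated 86% is therefore reachable, although the article gives no baseline rate. That power concerns arms, not single programmes.

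**Reliability of one programme's observed uptake.** With m = 50 and ICC = 0.01, m·ICC/(1 + (m − 1)·ICC) = 0.50/1.49 = 0.336. This does not depend on the uptake level. The remaining 66% of the between-programme variance is sampling error.

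**Size of the apparent lead, at an assumed mean uptake of 50%.**
- True SD between programmes: √(0.01 × 0.25) = 5.0 points.
- Sampling SD: √(0.99 × 0.25/50) = 7.0 points.
- Total SD: √(5.0² + 7.0²) = 8.6 points.
- The expected maximum of 24 is 1.948 SD, so the winner appears about 17 points above the mean. Its expected true lead is 0.336 × 16.8 = 5.6 points.
- If all 24 programmes were identical, the winner would still appear 1.948 × √(0.25/50) = 13.8 points above the mean.

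A beta-binomial simulation (24 programmes of 50, 40,000 replicates) agrees: observed lead 16.7 points, true lead 5.6, overstated by 11.1. The winner is truly the best 24% of the time and in the true top three 49% of the time.

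**Sensitivity.** The article fixes only the ICC of 0.01. The other ICCs and the uptake levels are assumptions.

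| ICC | Reliability | Winner is truly best (mean uptake 40-80%) |
|---|---|---|
| 0.01 | 0.336 | 22-24% |
| 0.02 | 0.505 | 30-34% |
| 0.05 | 0.725 | 42-49% |
| 0.10 | 0.847 | 48-61% |

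At ICC 0.01 the overstatement is 8 to 11 points over the same uptake range. At the 84.3% two-dose coverage quoted in the Introduction, p(1 − p) = 0.132. The apparent lead is then about 1.948 × √(0.0364² + 0.0512²) = 12 points, and the lead with no true differences is about 10.

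If one programme is truly 10 points better than 23 others at 50%, it is picked 33% of the time. At 20 points better, it is picked 81% of the time.

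**If only 12 programmes can be compared.** Wait-list delivery starts at 3 months, when the last stated assessment takes place. The stated schedule therefore shows no post-programme outcome for those 12 clusters. With the 12 intervention-arm programmes alone (ICC 0.01, uptake 50%), the best is picked 32% of the time and its lead is overstated by 9.3 points.

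**Infections detected.** If this is an observed count, its expected value is roughly participants × infection risk × the share of infections that are tested. At equal risk, a programme that doubles testing about doubles its count and ranks worse.

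**The case against.** Five arguments stand on the other side.

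*The choice is made through a simulation, and the text also speaks of models in the plural.* This is true. But the simulation is trained on the same programme results, which does not remove their sampling error, and the sentence that states the rule names one programme. The text also mentions changes in uptake patterns and offers the uptake number only as an example, so an adjusted comparison is not excluded. None is stated, however, and the rule as written does not contain one.

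*The infection count may be simulated.* This limits the point. A reader might infer that a programme that succeeds at testing is penalised whether the count is observed or simulated. The article does not support that. In a simulation, testing could be held constant, or earlier detection could reduce spread. The objection is shown only for an observed count.

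*True differences may be larger than the planned ICC implies.* Chance is the larger part only up to an ICC of about 0.02. Above that it is not. The variance between clusters would then still include differences that existed before the programme. The requirement of common core content also makes large programme effects less likely.

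*Picking second best does little harm.* This holds in part. Even at ICC 0.01 and 50% uptake the selected programme is truly about 5.6 points above average, so the rule beats an arbitrary choice.

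*The calendar effect is uncertain.* Stage 3 shows a three-month lag for each wait-list cluster within a two-year span. It does not show that all wait-list programmes run after all the others.

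**Conclusion.** The concern holds in a bounded form. At the protocol's ICC and cluster size, the stated rule names the truly best programme about 22-24% of the time for uptake of 40-80% (about 32% at 50% uptake if only 12 programmes have post-programme data). It overstates the lead by about 8-11 points. These figures assume exchangeable programmes of exactly 50. At ICC 0.05 the probability rises to 42-49%, so the statement that the winner is mostly chance should not be made without the ICC attached. Raw uptake also rewards pre-existing differences between sectors and clusters, which a larger ICC does not cure.

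Two consequences that a reader might infer are not in the article. It does not plan to publish an effect size for the selected programme. Nor will 20,000 residents receive the selected model: they receive pamphlets, while the toolkit goes to further organisations, of which about 200 of all kinds are to be approached.

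**What to change.** For programmes with both pre- and post-programme data, compare change in uptake in a mixed model adjusted for baseline uptake, sector and calendar period. Use the shrunken programme effects with their uncertainty as inputs to the simulation. With equal cluster sizes, shrinkage corrects the size of the lead but not the order. The better ranking comes from the adjustment, and the safeguard comes from stating the uncertainty. Report the probability that each programme is best, or the set not distinguishable from the best, and disseminate the pooled core package if none stands out.

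Replace the number of infections detected with a measure not driven by testing volume, such as simulated infections at a common testing rate. State how it is weighed against uptake.

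The cost is a little more analysis. Including all 24 programmes would also need a post-programme assessment of the 12 wait-list clusters, which the stated schedule does not show. The selected programme's apparent advantage will be smaller, and there may be no single winner.

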#### 7.2.3. Data Type, Data Processing and Analysis

Stage 1 will involve administrative processes for building the collaboration platform. No data will be collected at this stage. During Stage 2, quantitative data will be collected using a self-administered questionnaire. Qualitative data will also be collected through focus group interviews. The transcription of data will be done after the focus group interviews. During Stage 3, all data generated will be quantitative. The primary outcomes will be vaccination rates. It will be calculated as the number of participants who have been vaccinated over the total number of participants. Each participant’s vaccine uptake will be recorded by asking the participants to provide their COVID-19 vaccination record in the Vaccine Pass, or the paper vaccine certificate delivered by the HK government. The secondary outcomes will be the amount and frequency of early testing, the levels of acceptability for vaccination and early testing, and the changes in knowledge, attitude and behaviour towards COVID-19 protection and prevention, as determined by a self-administered questionnaire. The questionnaires will be designed based on the KAP model. The validity and reliability of the questionnaires will be assessed in advance.

During Stage 2, quantitative data from the pre- and post-programme evaluations will be analysed using a paired Student’s *t*-test for continuous variables and McNemar’s test for categorical variables. Qualitative data from the focus group interviews will be first organised by an experienced qualitative researcher. The transcripts will be coded and analysed in a systematic and iterative manner. Finally, themes and subthemes will be generated. During Stage 3, cluster RCT data will be analysed according to an intention-to-treat (ITT) principle. All participants who attend baseline assessment will be included in the ITT analysis. Within groups, changes at T_1_ and T_2_ time points will be compared with baseline (T_0_) data using a paired Student’s *t*-test or McNemar’s test, as appropriate. To compare the between-group differences in mean change from baseline to 3 months, as well as testing the time × group interaction effects between groups, linear mixed models will be adopted for analyses. The variables that are significantly different between groups at baseline will be used as covariates in the linear mixed models. Binary logistic regression models will be also used to examine the association between interventions and the main outcomes. Odds ratios will be calculated to determine the magnitude of the intervention effect.

## 8. Study 2

Digital Health Literacy on COVID-19 for All: Co-creation and evaluation of interventions for ethnic minorities and Chinese people with chronic illnesses in Hong Kong

This is the first DHL intervention to be developed with a community-based participatory research approach [37] and to be co-created with the stakeholders. It is essential to build up everyone’s capacity to access, understand and interpret the health information they receive and to make appropriate health decisions (i.e., DHL). Once they learn the skills or improve their ability to search for reliable health information and evaluate it in a critical manner, they can apply such skills and abilities to other health issues.

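### Study 1 chooses covariates by baseline significance tests instead of fixing sector and baseline vaccination status in advance; the power cost is small at the planned effect but large if baseline coverage is high

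*Protocol article*

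**What the plan says.** Study 1, Stage 3, is a cluster randomised trial with a binary primary outcome: whether each participant has been vaccinated, taken from vaccination records (section 7.2.3).

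For the analysis, the same section adopts linear mixed models for change from baseline to 3 months and for the time-by-group interaction. On covariates it says: "The variables that are significantly different between groups at baseline will be used as covariates in the linear mixed models". It then adds: "Binary logistic regression models will be also used to examine the association between interventions and the main outcomes", with odds ratios as the measure of effect. No covariate is named for the logistic models.

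On design, section 7.2.1 says: "For each sector, 8 clusters (400 participants) will be evenly divided into either the intervention group or the control group". The Stage 3 text confirms that allocation is done separately by sector: "there will be four clusters in both the intervention and control groups from the NGOs, schools and companies, respectively". Sector is therefore a randomisation stratum, but it appears in no Stage 3 model.

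**The concern.** After proper randomisation, any baseline difference between arms is due to chance. A p-value for that difference says nothing about whether the variable predicts the outcome, and prediction is what makes adjustment worthwhile. The stated rule can bring in a variable that does not matter and leave out one that does. The fitted model is also not known until the data are seen.

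The variable most worth fixing in advance is baseline vaccination status. The eligibility criteria in section 7.2.1 do not exclude people already vaccinated, and a vaccinated person stays vaccinated, so status at T0 largely determines status at T2. A logistic model of T2 status without it passes a chance difference in baseline coverage straight into the odds ratio and leaves predictable variation in the error term. Sector is the other obvious candidate, because the design uses it as a stratum.

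**Working it through.** **Inputs from the protocol.** Two-sided 5% level and intra-cluster correlation 0.01; 50 people per cluster; 4 v 4 clusters (200 v 200 people) per sector; 12 v 12 clusters (600 v 600) overall; 20-point target difference (section 7.2.1). Two-dose coverage of 84.3% (Introduction). The control-arm vaccination rate is not given.

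**The plan's own power figure.** The plan claims "86% power to detect a difference of 20% if there are 50 participants in each cluster and 8 clusters in each sector". The design effect is 1 + 49 × 0.01 = 1.49.
- For 20% v 40% in one sector, SE = √[(0.20×0.80 + 0.40×0.60) × 1.49/200] = 0.0546. The non-centrality is 0.20/0.0546 = 3.66, and a t-test on 6 df gives 86.0%.
- 60% v 80% gives the same. 37% v 57% gives 79.6%.
- Over control rates of 10% to 70% this method runs from 79.5% to 93.8%.

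So 86% is attainable without covariate adjustment and is not shown to be wrong.

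**How large an imbalance passes as non-significant?** Assume 40% vaccinated at baseline and a test that allows for clustering.
- Pooled: SE = √(2 × 0.40 × 0.60 × 1.49/600) = 0.0345, and 1.96 × 0.0345 = 6.8 points.
- One sector: SE = √(2 × 0.40 × 0.60 × 1.49/200) = 0.0598, giving 11.7 points.

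A test that ignored clustering would flag a pooled difference at about 5.5 points. The plan does not say which test is meant.

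**Cost at the planned 20-point effect.** These are cluster-level simulations of T2 status pooled over 24 clusters, with control uptake assumed to be 10% of the unvaccinated.

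| Assumed sector baselines | No covariate | Sector + baseline |
|---|---|---|
| 40/40/40% | 100% | 100% |
| 20/40/60% | 97.7% | 100% |

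Within a single sector (40% baseline, normal approximation) the figures are about 91% and 99.9%.

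**Cost if coverage is high.** At 84.3% coverage the largest possible gain is 100 − 84.3 = 15.7 points, so 20 points cannot be reached. Take 84% baseline and assumed uptake of 10% v 30% among the unvaccinated.
- Final rates are 0.84 + 0.16 × 0.10 = 0.856 and 0.84 + 0.16 × 0.30 = 0.888, a difference of 3.2 points.
- Unadjusted SE = √[(0.856×0.144 + 0.888×0.112) × 1.49/600] = 0.0235. Then z = 0.032/0.0235 = 1.36, and power ≈ Φ(1.36 − 1.96) ≈ 27%.
- Simulation agrees: 26–27% unadjusted, against 87–90% with baseline status and sector across repeated runs.

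The adjusted figure comes from runs in which clusters varied in baseline coverage but not separately in uptake, which favours adjustment somewhat.

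**Carry-over of chance imbalance.** At 84% coverage the SD of the chance difference in baseline vaccination is √(2 × 0.84 × 0.16 × 1.49/600) = 2.6 points, nearly as large as the 3.2-point effect. With 10% uptake in both arms, a 3-point head start at T0 leaves 3 × 0.90 = 2.7 points at T2. When the intervention arm starts more than 3 points higher (about 12% of simulated null trials), the unadjusted test rejects in about 18–22% and the prespecified model in about 5%. These rates are conditional on the imbalance; the unadjusted test's overall type I error stays near 5% when sectors share a common baseline.

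**The case against.** The other side has several sound points.

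- **The rule covers the linear mixed models only.** Those models analyse change from baseline and time by group, so an outcome's own baseline already enters. This stands. The power figures above concern the logistic comparison of T2 status.
- **For the logistic model the article is silent, and an analysis plan may list covariates.** This stands as far as it goes, and silence alone would not be a finding. The significance rule, however, is stated positively, and whatever replaces it should cover the primary outcome's model too.
- **Sector is balanced by design.** This stands. A reader might infer that leaving sector out leaves a sector imbalance between arms; with 4 v 4 clusters in each sector it does not. It costs precision and makes the test conservative: with baselines of 20/40/60% the no-covariate test essentially never rejected under the null.
- **The plan never says a non-significant test proves balance.** A reader might take the rule that way, but the text only says which variables become covariates.
- **The large power loss belongs to effects far below the design value.** The 3.2-point scenario is about one sixth of the planned 20 points. This stands, and the claim must be limited accordingly. The scenario is still relevant, because the protocol's own coverage figure would rule out a 20-point gain in a population like that. Whether the target itself is realistic is a separate question.

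**Conclusion.** The point holds in a limited form. Choosing covariates by baseline significance is a stated and unsound rule for a randomised trial, and neither sector nor baseline vaccination status is fixed in advance for the logistic model of the primary outcome.

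It would be tempting to conclude that most of the trial's power is lost. The documents do not support that as a general statement. At the planned 20-point effect the pooled loss is between nothing and about 2 percentage points under the assumed baselines. The loss is large, about 26% against 87%, only if coverage at entry is near 84% and the achievable effect is about 3 points. The uptake rates, the sector baselines and the actual coverage of recruits are all assumptions. The fault in the rule itself depends on none of them.

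**What to change.** In section 7.2.3:

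1. Delete the sentence that selects covariates by baseline significance.
2. State that the Stage 3 models will include sector, as the randomisation stratum, and the baseline value of the outcome being analysed, all prespecified. Where a mixed model already handles the outcome's baseline through change or repeated measures, say so.
3. State specifically that the logistic model for vaccination includes baseline vaccination status and sector.
4. Report baseline characteristics by arm descriptively, without significance tests.

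This costs a few sentences. Sector is known at randomisation, and vaccination records and a T0 assessment are already planned, so no extra data or participants are needed.

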#### 11.2.3. Study Design

The duration of each schoolchild’s involvement in the study will be 6 months, with assessments at baseline before the intervention (T1), immediately after the intervention (T2), at 3 months after the intervention (T3), and at 6 months after the intervention (T4). It is proposed that 12 schools will participate in the study every 12 months, and thus it will take 36 months to complete the intervention in 36 schools. Four months will be used for data cleaning, analysis and report writing. Data will be collected at four time-points, T1, T2, T3 and T4, to test the sustained intervention effect.

Randomisation: A large-scale stratified cluster RCT will be undertaken. Primary schoolchildren will be recruited via local conventional school clusters from 18 districts in Hong Kong, which have been chosen to provide a geographically representative sample. The cluster sizes will be equal across school clusters. We will select 36 primary schools and will randomly assign them to the intervention group or the control group in a ratio of 1:1. To adjust for age as a confounding factor, the schoolchildren from each school cluster will be separately drawn from lower grades (Primary 1 to 3) and higher grades (Primary 4–6). Therefore, we have designed a three-level hierarchical mixed model that is randomised at the third level. Here, a school is considered to be a level-3 cluster, the grades within a school are considered to be level-2 stratified units and the schoolchildren in our trials are considered as level-1 units [58].

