#### 11.2.5. Data Analysis

Descriptive statistics will be used to present all of the demographic, programme attendance and outcome data. Chi-square or independent sample *t*-tests (for categorical and interval data, respectively) will be used to identify the heterogeneity of demographic and baseline data in the two groups and settings. The effectiveness of the VRG-based educational intervention on the primary outcomes (the level of knowledge and practice, the bacterial loads and the detection rates of respiratory viruses) will be examined by linear mixed-effect modelling to compare changes in the primary outcome values of the intervention and control groups over time (from baseline to the two post-tests) on an intention-to-treat basis, using repeated-measures analysis of covariance, multivariate analysis of covariance and/or mixed modelling techniques.

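### Study 1's logistic regression for its binary primary outcome makes no provision for the randomised clusters (about 10.8% type I error at the planned ICC); Study 5's analysis text permits methods at odds with its own three-level model

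*Protocol article*

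**What the plan says.** **Study 1.** Section 7.2.2 (Stage 3) allocates whole clusters, each being the participants recruited by one research partner. Allocation is done separately among NGOs, schools and companies and gives 12 clusters per arm. Section 7.2.1 sizes the trial for this, "assuming an intra-cluster correlation of 0.01", and claims "86% power to detect a difference of 20% if there are 50 participants in each cluster and 8 clusters in each sector". Section 7.2.3 defines the primary outcome as the proportion of participants vaccinated, checked against vaccination records. For analysis, it assigns linear mixed models to mean change and the time-by-group interaction, with this covariate rule: "The variables that are significantly different between groups at baseline will be used as covariates". It then adds: "Binary logistic regression models will be also used to examine the association between interventions and the main outcomes". Odds ratios are to express the size of the effect.

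**Study 5.** Section 11.2.3 describes a "three-level hierarchical mixed model that is randomised at the third level", with school at level 3, grade stratum at level 2 and child at level 1. Section 11.2.5 begins with linear mixed-effect modelling but ends by allowing analysis "using repeated-measures analysis of covariance, multivariate analysis of covariance and/or mixed modelling techniques". It describes the period of comparison as "from baseline to the two post-tests". Section 11.2.3 schedules three assessments after the intervention (T2, T3, T4), and each objective in Section 11.1 is set at 6 months, which is T4.

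**The concern.** Standard logistic regression treats participants as independent. Study 1's sample size rests on the opposite assumption: members of one cluster are correlated, and the trial was enlarged to allow for it. If the analysis drops that assumption, the standard error of the log odds ratio is too small and the p-value is judged against the wrong reference. Section 12 applies p < 0.05 to all analyses with nothing to compensate. This affects the primary outcome.

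The covariate rule is a separate weakness in the same section. It lets chance imbalance decide the adjusted model, and it does not guarantee that sector, within which clusters are allocated, is included. It does not contribute to the error rate calculated below.

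In Study 5 the concern is contradiction. In their standard form, repeated-measures ANCOVA and MANCOVA have no school or grade level. An analyst could follow Section 11.2.5 to the letter and still depart from the design in Section 11.2.3. The count of post-tests also leaves it unclear whether T4, the time point of every objective, is in the comparison.

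**Working it through.** **Study 1: inputs (Sections 7.2.1 and 7.2.2)**
- Test level: "With conventional assumptions of a two-sided 5% significance level".
- ICC 0.01; m = 50 per cluster; 4 v 4 clusters per sector, 12 v 12 overall.

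**Study 1: the plan's own power figure**
- Design effect = 1 + (50 − 1) × 0.01 = 1.49.
- The control rate is not stated, so one must be assumed. At 20% v 40% in one sector (200 participants per arm), SE = √[(0.2 × 0.8 + 0.4 × 0.6) × 1.49 / 200] = √0.00298 = 0.0546, and 0.2 / 0.0546 = 3.66.
- A cluster-level t test with 8 − 2 = 6 degrees of freedom then has power 0.860, the stated 86%. The result at 60% v 80% is the same. Over control rates of 20% to 70% the power runs from 0.795 to 0.938.
- The figure is therefore reproducible with a calculation that respects the clusters.

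**Study 1: type I error if the cluster is ignored**
- Formula: 2[1 − Φ(1.96 / √design effect)].
- At ICC 0.01: 1.96 / √1.49 = 1.96 / 1.22 = 1.61, giving 0.108.
- Simulated logistic regression with beta-binomial clusters and an assumed 40% uptake gave 10.7%, both with 12 v 12 and with 4 v 4 clusters.
- Sensitivity, with assumed ICCs:

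| ICC | Design effect | Type I error |
|---|---|---|
| 0.005 | 1 + 49 × 0.005 = 1.245 | 7.9% |
| 0.01 (planned) | 1.49 | 10.8% |
| 0.02 | 1 + 49 × 0.02 = 1.98 | 16.4% |

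- Standard errors that ignore the cluster are too small by a factor of √1.49 = 1.22.

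**Study 5: the plan's own sample size (Section 11.2.1)**
- Inputs: d = 0.2; power 0.8; level 0.05, taken as two-sided; correlation 0.05 within a grade stratum and 0.01 between strata of a school; 30 children per stratum; 2 strata per school.
- Unadjusted n per arm = 2 × (1.960 + 0.842)² / 0.2² = 392.4.
- Design effect = 1 + 29 × 0.05 + 30 × (2 − 1) × 0.01 = 2.75.
- 392.4 × 2.75 = 1079.2 per arm; 1079.2 / 60 = 17.99, so 18 schools per arm; 2 × 18 × 60 = 2160, which matches exactly.

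**Study 5: if a single-level option were used**
- 1.96 / √2.75 = 1.96 / 1.66 = 1.18, giving a type I error of 0.237 for a continuous outcome (simulation 23.3%).

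**The case against.** The strongest reply concerns Study 5. A reader might infer that both trials plan analyses that ignore the cluster, and that 24% is Study 5's error rate. The documents do not support this. Section 11.2.3 states a model with school as the top level, and Section 11.2.5 opens with mixed-effect modelling. The single-level methods appear only as alternatives in an and/or list. This objection stands, and the 24% is a conditional worst case. It also cannot be extended to virus detection, because Section 11.2.1 sets its correlations for continuous outcomes.

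For Study 1 it can be said that the article calls these cluster RCT data, places the logistic models after linear mixed models, and is a condensed account whose full analysis plan may give the cluster terms. Part of this stands. A mixed model has random effects by definition, and not listing them in an article is no fault, so nothing is held against the linear mixed models on that ground. The logistic sentence is different. It names a model and an effect measure for the main outcomes, and the named model in its usual form assumes independence. The linear mixed models, described for mean change, do not supply the odds ratio.

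A reader might also apply Study 5's ICC of 0.05 to Study 1, which would make the inflation larger. Setting, population and outcome differ, and Study 1 states its own value, so that step is not justified.

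**Conclusion.** The point holds for Study 1 and should be corrected before analysis. Followed as written, the logistic regression of the primary outcome has about 10.8% type I error at a nominal 5%, roughly double. This assumes the planning ICC of 0.01, clusters of 50, and no cluster adjustment specified elsewhere. Over the assumed ICC range of 0.005 to 0.02 the rate is about 8% to 16%. Covariate adjustment could change the residual ICC, and with it the figure.

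For Study 5 the finding is an inconsistency between Sections 11.2.3 and 11.2.5, with a further mismatch in the number of post-tests. The stated three-level model, if used, does not have an inflated error rate on this account. About 24% would apply only to a continuous outcome analysed by a permitted method without a school level, at the planning correlations.

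**What to change.** **Study 1, Section 7.2.3.** Replace the logistic sentence with a mixed-effects logistic regression (available in SPSS, the package named in Section 12) or a GEE. Either should have the research partner as cluster, sector as a fixed effect, baseline vaccination status as a covariate, and a small-sample correction for 24 clusters. Replace the baseline-significance rule with these prespecified covariates. Define baseline status so that it does not by itself determine the outcome for participants already vaccinated at entry.

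**Study 5, Section 11.2.5.** Delete the repeated-measures ANCOVA and MANCOVA options and refer to the three-level model of Section 11.2.3. Change the reference to two post-tests to T2, T3 and T4, with the 6-month (T4) contrast as primary, in line with Section 11.1.

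**Cost.** Wording only. Study 1's confidence intervals widen by a factor of about 1.22 compared with an analysis that ignores the cluster, before any small-sample correction. That is the proper width. No change in sample size is needed for this fix, because both calculations already allow for clustering.
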